# Developing and testing a nurse-led intervention to support bereavement in relatives in the intensive care (BRIC study): a protocol of a pre-post intervention study

**DOI:** 10.1186/s12904-020-00636-8

**Published:** 2020-08-18

**Keywords:** Bereaved relatives, Complicated grief, Intensive care unit, Nurse-led, Palliative care, Study protocol

## Abstract

**Background:**

When a patient is approaching death in the intensive care unit (ICU), patients’ relatives must make a rapid transition from focusing on their beloved one’s recovery to preparation for their unavoidable death. Bereaved relatives may develop complicated grief as a consequence of this burdensome situation; however, little is known about appropriate options in quality care supporting bereaved relatives and the prevalence and predictors of complicated grief in bereaved relatives of deceased ICU patients in the Netherlands. The aim of this study is to develop and implement a multicomponent bereavement support intervention for relatives of deceased ICU patients and to evaluate the effectiveness of this intervention on complicated grief, anxiety, depression and posttraumatic stress in bereaved relatives.

**Methods:**

The study will use a cross-sectional pre-post design in a 38-bed ICU in a university hospital in the Netherlands. Cohort 1 includes all reported first and second contact persons of patients who died in the ICU in 2018, which will serve as a pre-intervention baseline measurement. Based on existing policies, facilities and evidence-based practices, a nurse-led intervention will be developed and implemented during the study period. This intervention is expected to use 1) communication strategies, 2) materials to make a keepsake, and 3) a nurse-led follow-up service. Cohort 2, including all bereaved relatives in the ICU from October 2019 until March 2020, will serve as a post-intervention follow-up measurement. Both cohorts will be performed in study samples of 200 relatives per group, all participants will be invited to complete questionnaires measuring complicated grief, anxiety, depression and posttraumatic stress. Differences between the baseline and follow-up measurements will be calculated and adjusted using regression analyses. Exploratory subgroup analyses (e.g., gender, ethnicity, risk profiles, relationship with patient, length of stay) and exploratory dose response analyses will be conducted.

**Discussion:**

The newly developed intervention has the potential to improve the bereavement process of the relatives of deceased ICU patients. Therefore, symptoms of grief and mental health problems such as depression, anxiety and posttraumatic stress, might decrease.

**Trial registration:**

Netherlands Trial Register Registered on 27/07/2019 as NL 7875, www.trialregister.nl

## Background

### Bereavement in the intensive care unit

The integration of bereavement care into the support services offered to relatives of intensive care unit (ICU) patients has been described and endorsed by national and international ICU societies [1–4]. When a patient is approaching death in the ICU, relatives need to make a rapid transition from focusing on the recovery of their beloved one to preparing for their unavoidable death. The actual risk of death depends on the underlying disease and may surpass 50% in high-risk ICU patients [5]. Withholding and/or withdrawing life-sustaining measures in those patients has become common practice preceding death among patients in ICUs worldwide, with frequencies varying within and between countries from 1.7 to 85% [6]. Death might occur within minutes to days after the initiation of withdrawing life-sustaining therapy [7]. Furthermore, the time of death is sometimes postponed, for example, in the situation of an organ donation procedure or to provide the relatives some extra time to say goodbye to their loved one. Therefore, a patient’s death in an ICU can have a strikingly guided character and is difficult to compare with the dying situations in other healthcare settings or at home [8]. Palliative care in this phase aims to improve the quality of dying and death with personalized attention to physical, social, psychological and spiritual dimensions of care and well-being [2, 9], using variable methods and care plans [10]. Supporting the bereavement process of relatives during the ICU admission of their dying loved one has been incorporated into the daily care offerings of professionals worldwide [9, 11]. However, a gap exists in adequate ICU-based studies evaluating family-centered experiences and long-term health outcomes of bereavement care other than ‘satisfaction’ after the death of an ICU patient [9].

### Long-term grief in bereaved relatives

Grieving, with intense feelings and behavior of mourning, is a normal emotional reaction to the loss of a meaningful loved one and refers to the transition from the experience of loss to the adaptation to it [12]. Grieving is not restricted to specific thoughts, feelings, and behaviors, nor is it restricted to a limited time period. Grief after a sudden and unexpected death of a beloved person in the ICU is going to be hard and will probably last longer than 6 months. A wide variety of phenomena impede the establishment of complicated grief, which is described as serious and persistent grief with adjustment problems in the long term [13]. The Diagnostic and Statistical Manual of Mental Disorders (DSM) 5th edition defines ‘persistent complex bereavement disorder’ while the International Classification of Diseases (ICD) -11 includes ‘prolonged grief disorder’ as practically the same diagnostic entity, differing merely semantically [14]. This disorder is, among other signs, characterized by intense symptoms of grief lasting for more than 6 months post-loss, separation distress, intrusive thoughts, and feelings of emptiness or meaninglessness [13]. A recent meta-analysis revealed a prevalence of approximately 10% for grieving disorders among bereaved adults in a general population [15] which could lead to negative health outcomes, increased medical service utilization, and economic cost due to absenteeism from work [16].

Relatives of deceased ICU patients may develop complicated grief as a consequence of the unpredictable and burdensome situation of losing their loved one. Therefore, complicated grief has been included in the Post Intensive Care Syndrome-Family (PICS-F) framework [17, 18]. Demographic variables such as gender, relationship status, and cultural background, might be associated with complicated grief [19, 20]. In addition, factors related to quality of dying and death, communication of staff, and bereavement care might impact the process of grieving for ICU relatives [21, 22]. However, little is known about the determinants and actual prevalence of complicated grief in bereaved relatives of deceased ICU patients. In two small single-center studies, the prevalence of complicated grief measured by the Inventory of Complicated Grief (ICG) ranged from 5% (two out of 41) [23] to 46% (six out of 13) [24]. A French multi-center study among the relatives of 475 deceased ICU patients reported an incidence of complicated grief assessed by the ICG in half of the respondents at 6 months (52%), which remained unchanged at 12 months [19]. The same study presented a decline in posttraumatic stress symptoms from 6 to 12 months, 44 and 36% respectively, as measured by the Impact of Event Scale-Revised (IES-R). Despite the robust study design, the generalizability of these results to other countries remains unclear due to cultural differences in end-of-life perspectives and subsequent bereavement care. To our knowledge only one study has measured the experiences of bereaved relatives in a Dutch ICU [8]. Among 51 respondents the most reported complaints were sleeping problems, while 86% returned to work and normal activities within 4–16 months. Although this study did not measure complicated grief nor symptoms of stress, it reflects the normal grieving reactions being hard and lasting for a longer period for bereaved relatives in the ICU [8]. Patients could die rapidly, resulting in a dignified death with a low burden of suffering and few signs of discomfort [6]. A Dutch study found that the quality of the dying and death process was perceived as being high by both care-givers and relatives [25]. Therefore, it is important to explore grief and the experiences with the quality of bereavement care in relatives of deceased ICU patients in the Netherlands compared to the existing international findings.

### Supporting relatives of deceased ICU patients

To support relatives during ICU admission, multidisciplinary ICU teams have previously developed supporting interventions in the bereavement process [21, 26, 27]. Effective communication between relatives and ICU professionals, professionals’ empathic attitudes, and personalized interactions are highly valued aspects of care in the relatives’ perspective, particularly during the dying and death process of the patient [26, 28]. These aspects may improve preparedness for the expected death and should be tailored to the relatives’ specific needs [29]. In addition, bereaved relatives may need follow-up services to discuss the patient’s suffering or distress, to find answers to any remaining questions regarding the death of their beloved one, to discuss their own feelings of loneliness and to explore their expectations for the future [30]. Relatives also reported a preference for more formal support for their emotional situation and psychological symptoms in the early bereavement period (< 6 months) [31]. According to a European study among ICU nurses from 18 countries, bereavement follow-up services vary between countries and ICUs, such as ‘viewing the dead patient in the unit’ (91%) and ‘a phone call at a certain timepoint’ (31.0%) [32]. This international group of experts suggested in their study to further explore the needs of the relatives, to test the efficacy of interventions in bereavement care and to develop guidelines for ICUs aiming to adequately deliver support to relatives during this difficult situation.

### Aim

The aims of the BRIC (Bereavement in Relatives in the Intensive Care) study for bereaved relatives of deceased ICU patients are: 1) to develop and implement a multicomponent nurse-led intervention, 2) to explore the experiences with bereavement care such as aspects of communication, quality of ding and death, and quality of support to relatives, 3) to determine the effectiveness of this intervention on complicated grief, anxiety, depression and posttraumatic stress and 4) to identify determinants and risk factors of complicated grief.

### Hypotheses

We hypothesize the following:
A newly developed multicomponent nurse-led intervention, including communication strategies, materials to make a keepsake, and a nurse-led follow-up service, improves the quality of experiences with bereavement care in the ICU from the perspectives of the bereaved relatives.Symptoms of complicated grief depression, anxiety and posttraumatic stress, decrease after implementation of the multicomponent nurse-led intervention.

## Methods

The BRIC study is a cross-sectional pre-post intervention study. Two different consecutive groups of bereaved relatives, cohort 1 and 2, will be approached to participate in a single-site study to compare complicated grief, anxiety, depression, posttraumatic stress and experiences with bereavement care. Cohort 1 will receive the standard of care, including ICU nurses’ presence and support for relatives, explanation of the process of dying and death, and empathic communication skills. Cohort 2 will receive additional bereavement support through a newly developed multicomponent nurse-led intervention.

### Setting

The study setting is a university hospital in the Netherlands with a 48-bed mixed ICU divided into four units.

### Study population

The study population consists of bereaved relatives after the death of an adult (age ≥ 18) ICU patient who fulfil all inclusion criteria and none of the exclusion criteria. Hospital records are used to identify the patients’ relatives, i.e., the first and second contact persons. Respondents will be selected using four criteria: 1) their loved one had died in the predefined period; 2) they were present during the ICU stay preceding death; 3) they have sufficient knowledge of the Dutch language (to read and understand information on the study and the questionnaires); and 4) they are considered legally responsible. Relatives with unknown contact details will be excluded.

### Methodology

This study protocol follows the Standard Protocol Items: Recommendations for Interventional Trials (SPIRIT) checklist [33]. The recommended schematic diagram detailing the schedule of enrolment, interventions and assessments is provided in Table 1. The study is non-blinded and non-randomized due to practical issues in the multicomponent intervention elements, which were applied intuitively and in a tailored fit to the relatives by ICU nurses.

**Table 1 Tab1:**
[figure not shown]
Schedule of enrolment, intervention, and assessments according SPIRIT figure

BRIC Bereavement in Relatives in the Intensive Care; −t_1_ Approach and enrolment of cohort 1; −t_1_ Approach and enrolment of cohort 2; t_0_ Baseline measurement; t_1_ 6 to 8 weeks post-loss; t_2_ 6 months post-loss; TGI-SR Traumatic Grief Inventory-Self Report Version’; HADS Hospital Anxiety and Depression Scale; IES-R ‘Impact of Events Scale-Revised’; CQI R-ICU ‘Consumer Quality Index Relatives in the ICU’; QODD ‘The Quality of Dying and Death questionnaire’

#### Procedure

Consecutive ICU patients dying in the ICU between January 2018 and March 2020 will be identified from the ICU database. Descriptive data such as age, gender, length of stay, cause of illness and date of death will be extracted. Eligible relatives will be approached by telephone, where they are informed about the study and invited to participate in a survey exploring their current health situation and experiences with the quality of bereavement care. If interested, contact details such as email or postal address will be gathered to send additional written information and an informed consent form. After receiving the bereaved relative’s signed consent form, questionnaires will be send according to the participants’ preference of a digital version of the questionnaires or paper version with a stamp-free envelope.

#### Multicomponent nurse-led bereavement support intervention

Based on existing (inter) national policies, facilities and evidence-based practices [34], we aim to develop a nurse-led support intervention with subsequent implementation in practice during the study period. This intervention is expected to include 1) communication strategies, such as an information leaflet on loss and grief [21], a condolence greeting card [35], and a checklist with relevant topics to discuss in the process of dying and death [26]; 2) materials to make a keepsake [32], such as a lock of hair and a fingerprint; and 3) a nurse-led follow-up service, such as a memorial meeting and telephone follow-up calls 4 months post-loss [36]. The intervention will be developed in a multidisciplinary collaboration, including intensivists, spiritual service and social workers. The nurses will be invited to extend the standard of care with elements of the intervention applied to the needs and values of the relatives, thus providing personalized bereavement support. This multicomponent nurse-led intervention will be developed in co-creation with bereaved relatives to maximize care according to their ideals and perspectives, and not solely built on professional beliefs. Therefore, the Dutch foundation ‘Family and patient Centered Intensive Care’ (FCIC) will be involved in the development process.

To strengthen the development and implementation of the intervention fidelity measures will be used which will help to understand whether planned intervention was effective [37]. Several methods can be used assessing the quality and include both acceptability of measures in relation to the needs of the stakeholders (bereaved relatives) and practicality of the measures in relation to applicability for the users (ICU professionals). The implementation evaluation of this complex intervention will be performed by applying the RE-AIM model; Reach, Efficacy, Adoption, Implementation and Maintenance. The RE-AIM model is an instrument that measures the total impact of an intervention and provides insight into causes for (in)efficacy. RE-AIM is widely used in public health research, and will support the applicability and dissemination of the study results [38]. Table 2 provides an overview of the RE-AIM model applied in the current study.

**Table 2 Tab2:** Overview of the RE-AIM model applied in the BRIC study

RE-AIM	Characteristics	Level	Data collection
Reach	Baseline characteristics	Individual	Demographic data cohort 1 and 2
	Inclusion rate	Individual	Medical files
Efficacy	Comparing the study outcomes (before, after; corrected for covariates)	Individual	Measurements in cohort 1 and 2
Adoption	Proportion of ICU professionals using intervention elements	Organizational	Self-composed questionnaire among ICU professionals
Implementation	Number of intervention elements received by relatives	Individual	Self-composed items added to questionnaire measured in cohort 2
	Experiences with implementation	Organizational	Self-composed questionnaire among ICU professionals
Maintenance	Long-term adoption of the intervention	Organizational	Semi-structured interview with ICU manager

#### Study cohorts and time points

Both cohorts will be performed in study samples of 200 relatives per group, all participants will be invited to complete questionnaires measuring complicated grief, anxiety, depression and posttraumatic stress. Cohort 1 includes all reported first and second contact persons of patients who died in the ICU in 2018, which will serve as a pre-intervention baseline measurement. Eligible relatives were approached from March to May 2019 (−t_1_) and participants received the questionnaires directly after they signed the consent form (t_0_). The intervention was conducted from June 2019 onwards. Cohort 2, including all bereaved relatives in the ICU from October 2019 until March 2020, will serve as a post-intervention follow-up measurement. Eligible relatives will be approached 12 weeks after the death of their loved one (−t_2_) and participants will receive the questionnaires directly (t_1_) and at 6 months (t_2_) after they signed the consent form. The study design and timeline is presented in Fig. 1. For each deceased patient, up to 3 relatives can be included in the study. This recruitment process has been shown feasible in a previous study [39].

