#### Statistical analysis

Power and feasibility: Baseline (retrospective; t_1_) and follow-up measurements (6 weeks; t_2_ and 6 months; t_3_) will be performed in study samples of 200 relatives per group. These numbers are feasible, starting from a mean of 325 ICU deaths each year in the study setting, given a (2x) 12-month inclusion period, an expected 1.5 loved one per death, and an expected inclusion rate of 50% at 6 weeks and a retention rate of 80% at 6 months. These numbers ensure an effect size of 0.5 with a GPower t-test for the ´difference between two independent means´ (1-β = 95%, *p* < .05, two-tailed, d = .5) [48].

Analyses: Descriptive statistics (e.g., means, medians, or proportions as appropriate) and Student’s T-test between pre-post groups on demographic variables (e.g., gender, age, educational level) and outcome measures (e.g., complicated grief, anxiety, depression, posttraumatic stress, experiences with care) will be used to present noticeable differences between the baseline and intervention groups. Missing data will be handled using the multiple imputation. The scores will be analysed based on original data, and when available, according to established cut-offs. All test will be bilateral and significance will be defined as *p* < .05.

To test the hypotheses repeated measure analyses of variance (ANOVA) will be conducted with time as the within-subject factor (pre- versus post-intervention) and group (cohort 1 and 2) as the between-subject factor. Cohen’s d will be calculated to present effect sizes if applicable. Hierarchical regression analyses will be performed to explore determinants and identify subgroups (such as gender, ethnicity, risk profiles, relationship with patient) of bereaved relatives in the ICU who are at particular risk of developing mental health problems (i.e., those with scores above established cut-offs). Covariates, such as reason of admission, severity of illness, cause of death, bereavement care, time to say goodbye and social support, will be included in the regression model. This model will be adapted for cluster effects to correct for multiple relatives per deceased patient.

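### Time since loss differs between the cohorts and is in no planned model, so the cohort contrast mixes the intervention with the natural course of symptoms: certain at t1, dependent on the reading at t2

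*Protocol article*

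**What the plan says.** All references are to the protocol article.

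- **Cohort 1** (Study cohorts and time points): "Cohort 1 includes all reported first and second contact persons of patients who died in the ICU in 2018". "Eligible relatives were approached from March to May 2019", and "participants received the questionnaires directly after they signed the consent form". This is the only measurement of cohort 1.
- **Cohort 2** (same section): "Eligible relatives will be approached 12 weeks after the death of their loved one". The first questionnaire (t1) follows directly, and the text can be read as placing the second (t2) 6 months after consent. The legends of Table 1 and Fig. 1 instead define t1 as 6 to 8 weeks and t2 as 6 months post-loss. Statistical analysis relabels the baseline as t1 and the two follow-ups (6 weeks and 6 months) as t2 and t3.
- **Analysis** (Statistical analysis): the hypotheses are tested by repeated-measures ANOVA with time (before or after the intervention) within subject and cohort between subjects. No covariate is named. A separate regression on determinants and risk groups adds "Covariates, such as reason of admission, severity of illness, cause of death, bereavement care, time to say goodbye and social support" and is adapted for several relatives per patient.
- **Natural course** (Long-term grief in bereaved relatives): the disorder is characterised by "intense symptoms of grief lasting for more than 6 months post-loss". A cited multi-centre ICU study "presented a decline in posttraumatic stress symptoms from 6 to 12 months, 44 and 36% respectively". The same study found complicated grief in 52% at 6 months, with no change at 12 months.

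**The concern.** The primary outcome (TGI-SR) asks about symptoms in the preceding month, so a score belongs to the moment of completion. If symptoms change with time since the death, two groups questioned at different distances from it will differ even when the intervention does nothing. Here the distance is built into the recruitment calendar, so a larger sample does not remove it.

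The bias can run both ways. If symptoms decline, an earlier measurement in cohort 2 hides a benefit between cohorts, while the natural fall from t1 to t2 within cohort 2 can be read as a benefit. The ANOVA does not separate these: no relative is measured both before and after the intervention, and cohort 1 has one measurement. The section on limitations does not mention the issue. The third aim, effectiveness, rests on this contrast.

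**Working it through.** **1. Time since loss in cohort 1.** Inputs: deaths 1 January to 31 December 2018; approach 1 March to 31 May 2019; one month = 30.44 days.
- Shortest: 31 December 2018 to 1 March 2019 = 60 days = 2.0 months.
- Longest: 1 January 2018 to 31 May 2019 = 515 days = 16.9 months.
- All 365 x 92 pairs of dates, equally weighted (assumption): mean 287.5 days = 9.446 months, SD 3.57 months; 21% under 6 months, 29% over 12 months, about 1% within 84 days.
- If relatives were instead approached in order of death date (alternative assumption): 5.0 to 13.9 months, same mean, none within 12 weeks.

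**2. Cohort 2 and the gap in means (9.446 minus cohort 2).**

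| Point | Source | Months post-loss | Gap |
|---|---|---|---|
| t1 | legends, 6 weeks | 42/30.44 = 1.38 | 8.1 |
| t1 | legends, 8 weeks | 56/30.44 = 1.84 | 7.6 |
| t1 | text, 12 weeks | 84/30.44 = 2.76 | 6.7 |
| t2 | legends | 6.00 | 3.4 |
| t2 | text, from consent at 12 weeks | 2.76 + 6 = 8.76 | 0.7 |

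**3. What a timing difference can do.** The plan states 200 per group for d = 0.5, 95% power, two-sided 0.05. The t-test needs 105 per group for that, so 200 is not reproduced by these inputs, but it is ample: at 200 the detectable d is 0.36. With no intervention effect, a timing difference worth d = 0.1, 0.2 or 0.3 (an assumed range) gives a significant cohort difference in 17%, 51% or 85% of studies.

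**4. The document's own evidence of drift.**
- Posttraumatic stress: (44 - 36)/6 = 1.33 percentage points per month. Taken as linear, this gives 3.446 x 1.33 = 4.6 points at t2 by the legends, or 0.686 x 1.33 = 0.9 points if t2 runs from consent. For t1 it gives 9 to 11 points, but that extends the slope to before 6 months, where the document has no data.
- Complicated grief: 52% at both 6 and 12 months, so no slope.

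**5. What adjustment costs.** Take 200 per cohort, cohort 2 all at one time point, no clustering and unchanged residual variance. With a linear term, the variance of the cohort effect is proportional to 1/200 + 1/200 + gap²/(200 x 3.57²), against 0.0100 unadjusted.
- t2 at 6 months: 0.0100 + 11.88/2549 = 0.0147; SE ratio √1.466 = 1.21.
- t2 at 8.76 months: 0.0100 + 0.47/2549 = 0.0102; SE ratio 1.01.
- t1 at 12 weeks: 0.0100 + 44.70/2549 = 0.0275; SE ratio 1.66.

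With a quadratic term, the cohort 1 part becomes v′(X′X)⁻¹v at the cohort 2 time, where X holds 1, t and t² for cohort 1. The ratios are then 1.21, 1.23 and 2.47. The detectable d at t2 becomes 0.36 x 1.21 to 1.23 = 0.44. At t1 it becomes 0.36 x 1.66 = 0.60 (linear) or 0.36 x 2.47 = 0.89 (quadratic), beyond the planned 0.5.

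**The case against.** **Adjustment is not excluded.** The covariate list is introduced as examples, the abstract promises adjusted differences, the RE-AIM table says the efficacy comparison is corrected for covariates, and date of death is extracted. A full list may sit in a document not shown. This stands as far as it goes. But the stated hypothesis test has no covariate, and the largest built-in difference between the cohorts is named nowhere.

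**The primary outcome may not drift.** A reader might carry the 44% to 36% fall over to complicated grief and quote a bias in SD units. The document does not support that: the fall concerns posttraumatic stress, and the same study reports complicated grief unchanged from 6 to 12 months (measured with the ICG, not the TGI-SR). This objection stands in full after 6 months. Before 6 months the document has no grief data either way.

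**The t2 gap may be small.** A reader might infer a fixed 3.4-month gap. If t2 runs from consent, it is about 0.7 months. Cohort 1's wide spread and the t1 mismatch remain.

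**The schedule has slipped.** Study status says cohort 2 recruitment was postponed. The article appeared on 18 August 2020, 140 days after 31 March 2020, so a 12-week approach had passed for every death in the stated window. Unless that window moves, t1 will be later and its gap smaller. The figures above describe the stated schedule only.

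**The cut-off is not a diagnosis.** The protocol uses a severity sum and calls the cut-off of 61 tentative and provisional. It would be too strong to say that a disorder is diagnosed too early. What remains is that t1 scores are taken before the period in the protocol's own definition has run.

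**Conclusion.** The concern holds in limited form. As written, the effectiveness contrast is confounded with time since loss. On the stated schedule this is certain at t1: mean gap 6.7 to 8.1 months, with almost no cohort 1 relatives at a comparable distance from the death, so adjustment there would be extrapolation. At t2 the cohorts overlap and adjustment is workable; the mean gap is about 3.4 or 0.7 months according to which passage governs.

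The range of 2 to 17 months rests on calendar dates alone. The mean, the shares and the gaps assume evenly spread deaths and approaches. No drift can be quantified for the primary outcome from this document. For posttraumatic stress it is 4.6 or 0.9 percentage points at t2, if the cited decline is linear and applies to this setting.

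A reader might also conclude that cohort 1 should be cut to relatives bereaved at least 6 months. The figures speak against this as the main analysis: under even spread the cohort 1 mean rises from 9.4 to 10.8 months, and the gap to a 6-month t2 widens from 3.4 to 4.8.

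**What to change.** 1. Reconcile the cohort 2 time points and their labels across the Table 1 and Fig. 1 legends, Study cohorts and time points, and Statistical analysis, including whether t2 runs from the death or from consent, and restate them for the postponed recruitment.
2. Compute days from death to questionnaire completion for every record.
3. For effectiveness, replace the unadjusted ANOVA with a regression of cohort 2 at t2 against cohort 1, with time since loss (linear plus quadratic, or a spline) and the clustering by deceased patient already planned. Keep all cohort 1 records.
4. Report t1 descriptively, and do not read the t1 to t2 change in cohort 2 as an effect.
5. As sensitivity analyses only, restrict to relatives bereaved at least 6 months, and to a window around the actual t2 timing.

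Cost: date of death is already extracted, so only the completion date and a rewritten analysis paragraph are needed. With a quadratic term the standard error rises by about 21 to 23% and the detectable d from 0.36 to about 0.44, before clustering, which is still below the planned 0.5. The wording should be settled before cohort 2 data are examined.

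### Cohort 1 covers deaths in a full calendar year and cohort 2 only deaths from October to March, so about half of any seasonal difference would enter the before-after contrast

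*Protocol article*

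**What the plan says.** Under Study cohorts and time points, the pre-intervention group is a full year: "Cohort 1 includes all reported first and second contact persons of patients who died in the ICU in 2018". The post-intervention group is a half-year: "Cohort 2, including all bereaved relatives in the ICU from October 2019 until March 2020, will serve as a post-intervention follow-up measurement". The abstract gives the same window for cohort 2.

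The feasibility paragraph under Statistical analysis assumes something else: "given a (2x) 12-month inclusion period".

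Under Methodology the study is described as non-randomised. Under Statistical analysis the hypotheses are tested by repeated-measures ANOVA with time and group as factors and no covariate named. A separate regression model has an open list of example covariates, including admission reason, illness severity and cause of death. Neither season nor month of death is listed. The abstract and the RE-AIM table (Table 2) promise an adjusted before-after comparison without naming season.

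The variable needed is already collected. Under Procedure: "Descriptive data such as age, gender, length of stay, cause of illness and date of death will be extracted". The limitations section does not mention the unequal calendar windows.

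**The concern.** In a non-randomised before-after study, any systematic difference between the groups other than the intervention is confounded with it. Here the cohort definitions themselves create one: a whole year is set against an autumn-winter half-year. Season could act through case mix, through pressure on staff, or through bereavement falling around the turn of the year. The article itself says that staff communication and bereavement care might affect grief, and that workload might affect what nurses deliver. It does not say that either varies by season.

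If outcomes do differ by season of death, part of that difference would be read as an intervention effect, or would mask one. A larger sample does not remove such a bias.

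**Working it through.** **Inputs from the article.** Cohort 1: deaths in January–December 2018. Cohort 2: deaths in October 2019–March 2020. Sample: 200 relatives per group, two-sided 5% test, planned d = 0.5. Feasibility: "starting from a mean of 325 ICU deaths each year in the study setting"; 1.5 relatives for each death; half of them included at 6 weeks, and 80% of those retained to 6 months.

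**1. The plan's own figure.** Yield over 12 months = 325 × 1.5 × 0.50 = 243.75, about 244 relatives. After 80% retention: 243.75 × 0.80 = 195, close to the stated 200. The figure of 200 therefore rests on 12 months per cohort. Over six months the same rates give 243.75 / 2 = 121.9 (about 122) at 6 weeks and 97.5 (about 98) at 6 months. So the feasibility paragraph and the cohort 2 window do not describe the same recruitment period.

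**2. Share of a seasonal difference carried over.** Let D be the mean difference in outcome between October–March and April–September deaths, and p the share of cohort 1 deaths in October–March. Cohort 2's share is 1, so

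bias in the cohort contrast = (1 − p) × D.

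With even spread, p = (31 + 28 + 31 + 31 + 30 + 31) / 365 = 182 / 365 = 0.499, so 1 − p = 0.501. If 50–60% of cohort 1 deaths fall in these months, 40–50% of D is carried over.

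**3. Size for assumed D.** The documents give no value. The last column is the chance that the nominal 5% test rejects with 200 per group and no true effect (two-sample t-test, clustering of relatives ignored).

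| Assumed D (SD) | Bias (SD) | Share of d = 0.5 | Rejection rate |
|---|---|---|---|
| 0.1 | 0.05 | 10% | 8% |
| 0.2 | 0.10 | 20% | 17% |
| 0.3 | 0.15 | 30% | 32% |

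**4. Cost of matching months.** Restricting cohort 1 to January–March and October–December 2018 leaves 200 × 0.499, about 100 relatives. Power at d = 0.5, again ignoring clustering, is 98.3% (100 versus 200), 95.8% (100 versus 122) or 93.8% (100 versus 98).

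**5. Can season simply be added as a covariate?** Cohort 2 has no April–September deaths, so a season coefficient can be estimated only within cohort 1. There I crossed every 2018 death date with every approach date from 1 March to 31 May 2019:

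| Cohort 1 deaths | Mean months since loss | Range or SD |
|---|---|---|
| January–March | 14.0 | 11.0–16.9 |
| October–December | 5.0 | 2.0–8.0 |
| October–March half, combined | 9.4 | SD 4.67 |
| April–September half | 9.5 | SD 1.94 |

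The autumn-winter half consists of the two ends of the time-since-loss range, and the summer half is the middle. The correlation of season with time since loss is −0.01, but with the centred square of time since loss it is 0.73. A season term beside linear time would therefore absorb curvature in recovery. As an illustration, I set the true season effect to zero and assumed decay that is exponential (3- or 6-month constant) or logarithmic. The fitted season coefficient is then 11–18% of the drop between 3 and 9.4 months.

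**The case against.** The strongest case against is that nothing in the documents shows grief, anxiety, depression or care experience to vary with season of death. The 0.1–0.3 SD range is assumed, so the 10–30% figures only restate that choice, and the direction is unknown. This stands: the imbalance is documented, but its effect is not.

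Second, the covariate list is open and the full analysis plan is not shown, so season is unnamed rather than excluded. Cause of death and illness severity are named and, if used in the cohort comparison, would absorb part of any case-mix route. This also stands, with the limit that the ANOVA testing the hypotheses names no covariates.

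Third, time since loss is a difference visible in the documents: roughly 2 to 17 months in cohort 1, against an approach at 12 weeks in cohort 2. Season is speculative beside it. That is fair. It is a separate problem, and matching months does not solve it.

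Two stronger readings are tempting and fail. A reader might infer that the whole of any autumn-winter difference would be credited to the intervention. It would not, because cohort 1 itself contains January–March and October–December deaths. A reader might also infer from the near-zero linear correlation that season can be adjusted for independently of time since loss. The correlation of 0.73 with the squared term shows otherwise.

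**Conclusion.** The point holds as an undeclared imbalance of unknown consequence. About half of any seasonal difference would enter the cohort contrast, assuming deaths and approach dates evenly spread over their windows. An assumed difference of 0.1–0.3 SD gives a bias of 0.05–0.15 SD. The documents do not support saying that such a bias exists, or in which direction it would run.

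The conclusion depends on the six-month window being the intended one. If the 12-month period in the feasibility paragraph is meant, the imbalance largely disappears. The Study status section says that cohort 2 recruitment is postponed; if the death window moves as a result, the imbalance must be reassessed.

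**What to change.** 1. Reconcile the cohort 2 window under Study cohorts and time points with the inclusion period in the feasibility paragraph. This is a text correction if one of the two is a slip. If recruitment is in fact extended to 12 months, it costs time.
2. If six months stands, pre-specify a sensitivity analysis with cohort 1 restricted to deaths in January–March and October–December 2018. Report it beside the full comparison and interpret any disagreement cautiously. It needs only the date of death already extracted. The price is precision: with about 100 against 200 relatives, the standard error of the standardised difference rises from √(1/200 + 1/200) = 0.100 to √(1/100 + 1/200) = 0.122, before clustering.
3. Use a season covariate only in a model that also adjusts flexibly (non-linearly) for time since loss, and acknowledge that the season term is informed by cohort 1 alone.
4. List the unequal calendar windows as a limitation, and say that matching months leaves the time-since-loss difference between cohorts untouched.
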